### Pilot Study

A pilot study will be carried out for the duration of a month with 20 subjects. The objective will be to evaluate the questionnaires’ complementarity, clarity, and understandability. The patients selected for the pilot study will meet the criteria for inclusion. Once the pilot has concluded, modifications to the questionnaires will be made if necessary. The possibility to create a leaflet for the handling of the MyPlan app and the time frame for patient assistance via the app will be discussed.

### Measurement Tools

The following measurement tools have been validated:

Patient Experience Questionnaire-15, adapted and validated for Spanish language [28,29]: this questionnaire will allow us to explore patients’ perception with regard to the educational process and their participation in the decision-making processes during their hospitalization.Morisky-Green Questionnaire [30]: this questionnaire will allow us to evaluate patients’ treatment adherence. It is comprised of 4 binary questions that will reflect the degree of compliance in patients as well as information regarding the causes of noncompliance.Positive Mental Health Questionnaire [31]: this scale evaluates mental health from a positive viewpoint. It is comprised of 39 items, which are distributed across 6 categories: personal satisfaction, prosocial attitude, self-control, autonomy, problem-solving and self-actualization, as well as interpersonal relationship skills. Their measurement is made via Likert-type answers with the following range: “always or almost always,” “frequently,” “sometimes,” and “never or almost never.” It is validated among the general population in favorable psychometric values, with global reliability of 0.88 and variance of 45%.Forms for collection of sociodemographic and clinical variables.

### Data Analyses

The statistical analysis will be made using Stata (version 15; StataCorp). It will consist of obtaining the differences between different data collections (24 hours after admission, upon discharge, and 25 days after discharge) for every variable considered in this project as a performance measurement of the intervention. Efficacy, effectiveness, and efficiency indicators will be based on the study of change from before the intervention to after the intervention (ie, before the intervention; upon discharge; and the last control, 25 days after discharge at home). These will be based on relative indexes (ie, change percentages) and reliable change indexes (ie, Jacobson-Truax coefficient as well as alternative indexes, such as Tsu, Hagerman-Arrindell, and Speer-Greenbaun indexes). The difference in quantitative measurements in different phases will be based on factorial analysis (ANOVA). These will provide the main effects of change for all different phases. They will also provide the reliability intervals of the averages and the differences of proportion as measures to be assessed, as well as that of standardized indexes, such as Cohen *d*.

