### Objectives

The primary objective of this study is to evaluate the effectiveness of a pharmacological educational nurse intervention with MyPlan app in the experience of medical assistance, pharmacological treatment adherence, and positive mental health of patients with femur fractures at the Hospital Clínic de Barcelona. We also intend to compare the pre-post intervention effectiveness in the study variables 24 hours after admission, upon discharge, and 25 days after hospital discharge.

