### Design

This protocol describes a nonrandomized, quasi-experimental study with a pretest-posttest control group.

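### The design is labelled pretest-posttest with a control group, but Data Analyses rests effectiveness on before-after change and the main effect of phase, and names no contrast with controls

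*Protocol article*

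**What the plan says.** The Design section reads "This protocol describes a nonrandomized, quasi-experimental study with a pretest-posttest control group", and the Methods paragraph of the Abstract gives the same design. Data Analyses then sets out the analysis in four statements:

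- On its content: "It will consist of obtaining the differences between different data collections (24 hours after admission, upon discharge, and 25 days after discharge", applied to every variable used to measure performance.
- On the effectiveness measures: "Efficacy, effectiveness, and efficiency indicators will be based on the study of change from before the intervention to after the intervention".
- On their form: "These will be based on relative indexes (ie, change percentages) and reliable change indexes".
- On the model: "The difference in quantitative measurements in different phases will be based on factorial analysis (ANOVA", followed by "These will provide the main effects of change for all different phases".

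The section closes with interval estimates for means and for differences of proportions, and with Cohen d. It does not say whether these are between groups or over time. The word control appears in Data Analyses only as a name for the last follow-up visit. The Objectives section adds "We also intend to compare the pre-post intervention effectiveness in the study variables 24 hours after admission, upon discharge, and 25 days after hospital discharge".

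**The concern.** In a pretest-posttest control group design, the controls show what would have happened over the same period without the intervention. The intervention effect is therefore the difference between groups in change (the group-by-phase contrast), or the group difference at follow-up adjusted for baseline. The main effect of phase is the average change over time across everyone analysed. It adds together the intervention effect and whatever else moves the scores: recovery, repeated completion of the same questionnaires, and regression to the mean. It cannot separate them.

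The baseline is taken 24 hours after admission with a femur fracture. The Intervention section itself expects patients to feel sad and frustrated in hospital, and to see pain and mobility improve from day to day. Some change in positive mental health without any intervention is therefore foreseeable. If effectiveness is judged on change over time, the control group plays no part in the conclusion, and the effectiveness claims in the Objectives and Conclusions are not supported by the planned estimate.

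**Working it through.** **1. Design against analysis.**

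| Element | What the article states |
|---|---|
| Design (Abstract, Design) | Nonrandomized, pretest-posttest, control group |
| Effectiveness indicators (Data Analyses) | Change from before to after |
| Indexes (Data Analyses) | Percentage change and reliable change |
| ANOVA result (Data Analyses) | Main effects of phase |
| Group factor, group-by-phase term, comparison with controls | None named |

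**2. What each contrast estimates.** Let the average change without intervention be T in both arms and the intervention effect be E.

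- Change within the intervention arm: T + E.
- Change pooled over two equal arms (main effect of phase): T + E/2.
- Difference in change between arms (group-by-phase): (T + E) − T = E.

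Only the third is free of T. With E = 0, the first two still estimate T.

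**3. Illustration of size.** The article gives no figure for T and none for the pre-post correlation, the allocation ratio or the arm sizes, so there is no figure of its own to reproduce here.

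From the article: total sample 278 and 15% loss (Participant Selection and Recruitment).

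Assumed: 1:1 allocation, E = 0, equal SDs at both times, pre-post correlation r = 0.6, T = 0.2 or 0.3 SD, and a two-sided 5% paired t-test on a quantitative score.

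Completers per arm: 278 / 2 × 0.85 = 118; both arms together: 236.

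Noncentrality of the paired t-test = T / √(2(1 − r)) × √n, with √(2 × 0.4) = 0.894.

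- n = 118, T = 0.2: 0.2 / 0.894 × 10.86 = 2.43, rejection about 67%.
- n = 118, T = 0.3: 0.3 / 0.894 × 10.86 = 3.64, rejection about 95%.
- n = 236 (pooled over arms), T = 0.2 and 0.3: 3.43 and 5.15, rejection about 93% and 99.9%.

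**4. Sensitivity to the assumptions.** Simulation with 118 per arm, 3,000 trials per setting, E = 0 and equal change in both arms. Ranges are over r = 0.3 to 0.7.

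| Natural change T | Within-arm pre-post test significant | Pooled phase effect significant | Between-arm difference in change significant |
|---|---|---|---|
| 0 | 4% to 5% | 4% to 5% | about 5% |
| 0.1 SD | 15% to 29% | 26% to 51% | 5% to 6% |
| 0.2 SD | 45% to 80% | 73% to 98% | about 5% |
| 0.3 SD | 77% to 99% | 97% to 100% | 4% to 6% |

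The first two tests depend strongly on T, and the third does not. With T = 0 all three are at their nominal level, so the problem arises only where scores move without the intervention.

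**The case against.** The strongest defence is that Data Analyses does not exclude the control group. A factorial ANOVA normally has more than one factor, and in this design the natural second factor is group. Differences of proportions and Cohen d could also be between-group quantities. A change score is not uncontrolled in itself: comparing change between arms is a standard analysis. The Objectives introduce the pre-post comparison as an addition to the primary objective, and a condensed article may leave model terms to a fuller document.

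Part of this stands. A reader might infer that group never enters the analysis, or that every planned estimator is a within-patient contrast. The text does not support that, because the factorial model, the proportions and Cohen d leave room for a group factor. What the defence does not remove is that the section states positively what the analysis consists of, what the effectiveness indicators rest on and which ANOVA effect is the result, and none of these is a contrast with controls. A fuller plan that followed these statements would inherit the problem.

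A reader might also infer that the study will probably declare an ineffective intervention effective. The documents do not support that forecast. They give no baseline level, SD, correlation or expected change for any outcome. Foreseeable change without intervention has textual support at most for positive mental health. Nothing in the article says that Morisky-Green adherence rises as a fracture heals, or that patient experience scores are depressed at 24 hours. The paired t-test illustration also does not represent an adherence scale made of four binary questions.

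Finally, the article cannot settle whether the fault lies in the analysis or in the design label. Apart from that label it gives no allocation, care or size for a control group, and the Intervention and Procedure sections describe only patients who receive the app and the sessions.

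**Conclusion.** The point holds as a mismatch between the stated design and the stated analysis, and it should be corrected. The main effect of phase and before-after change cannot isolate the intervention from time, and no contrast with controls is named. Confidence is high on that.

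The size is illustrative. Under 1:1 allocation, 15% loss, no intervention effect and correlation 0.6, natural change of 0.2 to 0.3 SD makes a within-arm pre-post test significant in about 67% to 95% of trials, against a nominal 5%. The between-arm difference in change stays near 5% provided both arms change equally. At 0.1 SD the within-arm figure is only 15% to 29% over correlations of 0.3 to 0.7. The protection from the between-arm contrast also depends on comparable groups, which a nonrandomized design does not guarantee; hence the need for adjustment.

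**What to change.** In Data Analyses, name the between-group difference as the effectiveness estimate, at discharge and at day 25, with 95% CI. This can be the group-by-phase contrast, or the group difference adjusted for the baseline score and the background covariates already listed under Demographics and Baseline Functioning. Covariates should be restricted to those fixed before the intervention; that list also contains time of hospitalization and adverse effects, which can arise after it starts. If adherence is analysed as a binary outcome, use a corresponding binary-outcome model with the same group contrast. Label within-group change, percentage change and reliable change indexes as descriptive.

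If controls are being enrolled and measured at the same three times, this costs only rewording and needs no new data. If no control group is enrolled, correct the design label in the Abstract and the Design section, and limit the effectiveness claims in the Objectives and in both Conclusions to uncontrolled before-after change. That costs no data either, but it narrows what the study can claim.

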## Results

Enrollment was initiated in October 2022 and will be completed in April 2023.

The main contribution of this protocol is a detailed description of a nursing intervention with the support of a smartphone app that will generate knowledge about patients’ experiences, their adherence, and their positive mental health. The protocol is registered with ClinicalTrials (NCTT05669040).

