**Methods:**

A nonrandomized, quasi-experimental study will be carried out with a pretest-posttest control group. It will include 278 older patients diagnosed with femur fractures, with a Glasgow Coma Scale of 15 and access to mobile devices. Patients with psychological pathologies and cognitive impairment or patients treated in isolation will be excluded. Study variables are as follows: sociodemographic variables (AdHoc Form), patient experience (Patient Experience Questionnaire-15), adherence to pharmacological treatment (Morisky-Green questionnaire), and positive mental health (Positive Mental Health questionnaire). The measurements will be taken 24 hours after admission, upon discharge, and 25 days after discharge.

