**Results:**

Enrollment commenced in October 2022. Data collection will be completed in April 2023.

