### Scope of Study

This project estimates the application of this approach in the Institute of Traumatology and Orthopedics of the Hospital Clínic de Barcelona between October 2022 and April 2023.

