### Participant Selection and Recruitment

Eligible participants will be identified in the hospitalization unit through the observation of a census by the principal investigator (PI) with a nonprobabilistic sample (according to the patients’ willingness to participate).

The sample calculation will be made by taking into account the total number of patients treated in the traumatology service for a femur fracture diagnosis during 2020. Approximately 494 patients are admitted annually with a femur fracture diagnosis. GRANMO software (version 7.12; IMIM Medical Informatics Unit) will be used with a 95% CI and a maximum indeterminacy of *P*=.5, accounting for a 15% loss, for a final recommended sample of 278 subjects to ensure a sufficient sample size for the analysis of the different variables.

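### At about 494 admissions a year, 278 patients are not credibly deliverable between October 2022 and April 2023, and enrolment and data collection end in the same month despite a day-25 outcome

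*Protocol article*

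**What the plan says.** All statements are in the protocol article.

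- **Source population** (Participant Selection and Recruitment): "Approximately 494 patients are admitted annually with a femur fracture diagnosis". The count is tied to 2020 and to one traumatology service.
- **Target** (same section): the calculation is made "with a 95% CI and a maximum indeterminacy of" one half, "accounting for a 15% loss, for a final recommended sample of 278 subjects".
- **Site and window** (Scope of Study): "Institute of Traumatology and Orthopedics of the Hospital Clínic de Barcelona between October 2022 and April 2023".
- **Enrolment** (Results section): "Enrollment was initiated in October 2022 and will be completed in April 2023".
- **Data collection** (abstract, Results): "Enrollment commenced in October 2022. Data collection will be completed in April 2023".
- **Outcome times** (abstract, Methods): "The measurements will be taken 24 hours after admission, upon discharge, and 25 days after discharge". Under Procedure, patients are contacted through the app at day 25 to complete the questionnaires, and access closes at day 30.
- **Filters** (Participant Selection and Recruitment; Inclusion and Exclusion Criteria): participation is voluntary. Patients need a Glasgow score of 15, Spanish and a mobile device. Psychological pathology, cognitive impairment and isolation exclude.
- **Pilot** (Pilot Study): "A pilot study will be carried out for the duration of a month with 20 subjects". The article does not say whether that month or those patients fall inside the main study.

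**The concern.** Target, admission rate, window and follow-up time are all printed, and they do not fit together. Seven months at this rate give barely more admissions than the target, yet the eligibility criteria and voluntary participation must remove some of them. Enrolment and data collection also finish in the same month, although the last outcome falls 25 days after discharge.

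Two things are at stake. The article presents 278 as enough to analyse its variables, and that assurance fails if the window yields far fewer. And patients enrolled late would lack the final outcome because of the calendar rather than for reasons of their own.

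**Working it through.** **The plan's own figure.** The precision behind 278 is not given, so it cannot be strictly reproduced. With the finite-population formula n = N·z²·p·q / [d²(N − 1) + z²·p·q], N = 494, p = 0.5 and z = 1.96:

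- at an assumed d = 0.05, n = 474.4 / 2.193 = 216.3, so 217, and 217 / 0.85 gives 256;
- d of about 0.046 gives n of about 236, and 236 / 0.85 gives 278.

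The feasibility check does not depend on this and takes 278 as stated. Completers implied by 15% loss: 278 × 0.85 = 236.3.

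**Supply over the longest window.** 1 October to 30 April is 212 days. The rate is 494 / 365 = 1.353 a day. A day-25 measurement by 30 April needs discharge by 5 April (187 days). Length of stay is not given. At least 4 weekday sessions imply about 4 days or more, which leaves 183 days of admissions.

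| Quantity | Calculation | Result |
|---|---|---|
| All admissions | 1.353 × 212 | 286.9 |
| Able to reach day 25, zero stay | 1.353 × 187 | 253.1 |
| Able to reach day 25, 4-day stay | 1.353 × 183 | 247.7 |

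**Demand against supply, like for like.**

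- Enrolled against admitted: 278 / 286.9 = 97%.
- Completers against completable: 236.3 / 253.1 = 93%, and 236.3 / 247.7 = 95%.

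These shares precede every exclusion and refusal. Dates are given only by month, and shorter readings are worse: 1 October to 1 April is 183 days, or 247.7 admissions in all, fewer than 278.

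**Late patients.** If enrolment is uniform to 30 April, the share with no day-25 measurement by that date is:

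- zero stay: 25 / 212 = 11.8%;
- 4-day stay: 29 / 212 = 13.7%;
- 8-day stay (assumption, counting admission and discharge days, so admitted by 29 March, day 180): 32 / 212 = 15.1%.

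Of 278 patients that is 278 × 0.118 = 33 to 278 × 0.151 = 42. The whole 15% allowance is 278 − 236.3 = 41.7 patients.

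**Illustration.** Suppose 40% to 60% of admissions are eligible and consent (assumption; the article gives no rate).

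- Enrolled over the full window: 0.40 × 286.9 = 115 to 0.60 × 286.9 = 172.
- Counting only those admitted by 29 March: 1.353 × 180 = 243.6, so 97 to 146.
- Time to enrol 278: 12 × 278 / (494 × 0.60) = 11.3 months, to 12 × 278 / (494 × 0.40) = 16.9 months.

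**The case against.** A reader might set 278 against the 253 admissions that could complete follow-up and conclude that the target is arithmetically impossible. The documents do not support that. The 278 is a gross figure that already contains 15% loss, so not every enrolled patient needs day-25 data. Like for like, 278 is below 287 and about 236 is below 253. This objection stands, and the claim here is limited to practical deliverability.

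A reader might also infer that the late patients are lost in addition to the planned 15%. The article does not say what the 15% covers, so adding the two is not established. What stands is that the calendar alone could use up most of the allowance, or all of it with an 8-day stay.

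The 494 is approximate and rests on 2020. If admissions were 20% higher (assumption, about 593 a year), 278 would still be 278 / 344.3 = 81% of all admissions, and 236.3 completers would be 78% to 80% of those able to reach day 25 (303.7 and 297.2). That is still before exclusions and refusals, so this uncertainty does not rescue the plan.

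An article condenses its protocol, but nothing here depends on omitted detail. No loss of power is quoted, because the article gives neither group sizes nor a power target.

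**Conclusion.** The point holds in this form: the stated size is not credibly deliverable in the stated window. It needs about 97% of all admissions enrolled, and completers equal to 93% to 95% of those who could reach day 25, before any selection. This rests on the printed rate, the longest reading of the dates and a stay of 0 to 4 days, all favourable to the plan.

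Separately, the two April 2023 end dates conflict with the follow-up schedule if enrolment runs through April. About 12% of patients, more once length of stay is counted, would have no day-25 outcome by the close. The figures of 97 to 172 patients and 11 to 17 months are illustrations under assumed uptake; the conclusion does not need them. The effect of the pilot cannot be sized, because its timing is not stated.

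**What to change.** 1. Take the eligibility and consent rate observed so far. Then either restate the target, with the precision it gives, as what the window can yield, or move the enrolment end date to one that fits 278.
2. State separate dates for the end of enrolment and the end of data collection. Place the second after the last enrolled patient's day-25 questionnaire, with response time up to the day-30 close described under Procedure.
3. State whether the 20 pilot patients count towards the target and whether the pilot month lies inside the window.

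The cost is restated dates or a restated number in the protocol and the registry entry. More calendar time is needed if 278 is kept; at a lower target, only enough to follow late patients to their last questionnaire. Patient care does not change.

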## Discussion

### Expected Findings

One of the strong points of this study is the linear evaluation of the intervention (ie, 24 hours after admission, upon discharge, and 25 days after discharge), which can demonstrate the effectiveness of assisting the patient throughout the process. Another important finding may be related to the impact of the intervention on the quality of care because it could contribute to early detection and prevention of medication errors, minimizing both the associated complications that these patients may have and hospital re-admissions. Finally, another potential strength of the study is that the intervention can be extrapolated to different specialties in the hospital, which would contribute to the improvement of care for all patients.

The main result will be to generate a change in the medication administration process, implementing the nursing pharmacological education intervention. The secondary result will be related to the patient's hospital experience, the increase in treatment adherence, and the improvement of positive mental health. The expectation is to generate patient empowerment and a reduction in the number of consultations and hospital admissions derived from some adverse effects of the pharmacological treatment.

